**Methods:**

KlimaNot is a multicenter, registry-based observational cohort study with retrospective and prospective components. The primary analysis is a prespecified retrospective evaluation using routinely collected encounter data from the German National Emergency Department Data Registry (AKTIN), comprising approximately 6.35 million ED visits from up to 56 EDs (2019-2024). Hospital-level environmental exposures (eg, temperature and selected air pollutants) will be linked to each participating ED based on location and summarized to daily metrics. The primary endpoint is daily all-cause ED visit volume at the hospital-day level. Secondary endpoints include hospital admission probability, syndromic and diagnostic case-mix, referral source and mode of transport, and routinely recorded proxies of clinical severity (eg, triage acuity). Heat effects will be quantified using models allowing for nonlinear exposure–response relationships and delayed (lagged) effects, with adjustment for site, seasonality and time trends, weekday, and public holidays; effect modification by age, sex, multimorbidity proxies, and area-level socioeconomic deprivation will be assessed. Additional analyses include a predefined case study for the region Stuttgart, leveraging extended longitudinal and more detailed pathway data, development and validation of heat-sensitive syndromic surveillance indicators, evaluation of short-term forecasting models of ED usage, and an ancillary prospective geriatric substudy collecting patient-reported and functional outcomes to better characterize vulnerability in the oldest-old.

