#### Routine ED Records

Retrospective data will be sourced from the AKTIN Registry [27]. The registry is implemented on the underlying AKTIN infrastructure, a nationwide federated data network operated within the Network University Medicine [28]. For the study, a total of 56 EDs throughout Germany, including clinics of different care levels in cities with different population sizes, provide electronic health records from all ED visits documented in the respective ED in the years 2019 to 2024.

Across participating EDs, approximately 6.35 million ED visits will be available for the study period, with an anticipated exclusion of up to 10% due to missing key variables. This retrospective ED dataset contains patient-specific information on age, sex (male, female, or other), and the zip code of the patient’s place of residence, as well as administrative data on mode of transport to the ED, time of admission, and mode of disposition (discharge to home, transfer to other hospital, inpatient admission, or death). Furthermore, it contains the following treatment information: ED diagnoses in the form of *ICD-10-GM* (*International Classification of Diseases and Related Health Problems, Tenth Revision, German Modification*) codes with a labeling of the main ED diagnosis, additional information on diagnosis certainty (secured, suspicion of, condition after or exclusion of diagnose), chief complaint in the form of Canadian Emergency Department Information System – Presenting Chief Complaints (CEDIS-PCL) codes, urgency level coded as Manchester Triage System (MTS) or Emergency Severity Index (ESI), vital parameters, Glasgow Coma Scale (GCS) and isolation status [29-31]. In case of an inpatient admission following the ED visit, inpatient treatment information according to the German social laws regulating the billing of inpatient services (§ 21 Krankenhausentgeltgesetz, KHentG) is available. This information contains the inpatient discharge diagnosis, also coded as *ICD-10-GM*. Multiple ED visits by the same person during the study period cannot be attributed due to data protection requirements.

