### Data Linkage

The linkage between patient data and environmental data is established at the hospital level. For each hospital, the nearest weather station with the smallest air distance is identified, ensuring that there are fewer than 500 missing values within the time interval of 2019-2024. Due to the limited spatial availability and completeness of air quality data, air data are matched solely based on proximity to the hospital, accepting some missing values. Both the weather and air quality data are provided as hourly records, as well as in a summarized format with daily minimum, maximum, and mean values. The spatial granularity is selected to be as fine as possible. However, a finer granularity is not feasible due to data policy restrictions on patient data and the limitations of the environmental measurement grid. Under the assumption that environmental phenomena generally occur on a large scale and that most patients choose the nearest ED in case of an emergency, the linked data provide at least an approximate overview of the environmental influences to which patients were exposed before the onset of their illness. Following scientific best practices and ensuring reproducibility, the Python code used for the data linkage is publicly available on GitHub [35]. The pollen stations will be selected in consultation with experts from the PID, considering data completeness as well as proximity to the ED (Figure 1).

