#### Statistical Modeling of Environmental Factors on ED Visits (O1-5)

The number of all-cause ED visits in relation to temperature and environmental factors will be investigated using a 2-stage analysis approach. In the first stage, given the available data, we plan to fit the site-specific number of daily ED visits using a quasi-Poisson regression model including a distributed lag nonlinear model for daily temperature to capture delayed temperature effects, using appropriate splines and lags [34].

These models aim to adjust for seasonal trends in temperature and air quality using smooth functions and will additionally include day of week, public holidays, and further covariates (O₃, NO₂, particulate matter [PM10 and PM2.5], SO_2_, UV-A, UV-B radiation, and predefined pollen). Heat days, one of the main focuses of this study, will be defined a priori based on clinic-specific temperature distributions (days with mean air temperature above the 95th percentile), and alternative operationalizations (eg, heat index, tropical nights, and heatwaves) will be examined in prespecified sensitivity analyses. The analysis is planned to be stratified by age group (0-5 years, 6-11 years, 12-17 years, and ≥65 years). In the second stage, ED-specific distributed lag nonlinear model coefficient vectors are planned to be pooled using a random-effects meta-analysis approach to obtain an overall heat exposure–response association and to quantify between-site heterogeneity [34]. As sensitivity analysis, we will assess the robustness of our modeling choices, including alternative lag windows, splines, and alternative number of knots for temperature and lag. We will also investigate the sensitivity when using other alternative stratification strategies and missing data handling. A detailed statistical analysis plan will be prepared in advance of the data analysis.

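### The pooled primary heat effect will have too narrow a confidence interval if EDs' same-day residuals stay correlated after adjustment; the planned second stage neither checks nor allows for this

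*Protocol article*

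**What the plan says.** The section Statistical Modeling of Environmental Factors on ED Visits (O1-5) sets out two stages.

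- **Stage 1:** "we plan to fit the site-specific number of daily ED visits using a quasi-Poisson regression model including a distributed lag nonlinear model". On adjustment: "These models aim to adjust for seasonal trends in temperature and air quality using smooth functions and will additionally include day of week, public holidays". Pollutants, UV radiation and selected pollen are listed as further covariates.
- **Stage 2:** "ED-specific distributed lag nonlinear model coefficient vectors are planned to be pooled using a random-effects meta-analysis approach", in order "to obtain an overall heat exposure–response association and to quantify between-site heterogeneity".

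The sensitivity analyses named there vary lag windows, splines, knots, stratification and missing-data handling. None concerns dependence between EDs. Further detail is left to a statistical analysis plan that is not shown.

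Two other places bear on the point. Under Routine ED Records, the 56 EDs "provide electronic health records from all ED visits documented in the respective ED in the years 2019 to 2024". Under Data Linkage, "For each hospital, the nearest weather station with the smallest air distance is identified", and the linkage is defended "Under the assumption that environmental phenomena generally occur on a large scale".

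**The concern.** The data are ED by calendar day, crossed: every ED is observed over the same dates. Separate site fits give a covariance matrix within each ED and none between EDs. A random-effects meta-analysis of those fits therefore treats the EDs' sampling errors as unrelated unless a further step is added, and none is named.

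Suppose demand moves up or down in many EDs on the same date for a reason that stage 1 does not model. If those dates are heat days in many EDs, the heat estimates move together. The quasi-Poisson dispersion does not capture this, because it works within one ED. The random-effects variance does not capture it either, because a shared error shifts all estimates alike and adds nothing to their spread.

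There is some reason to expect such residual movement. Smooth time terms cannot absorb single-day shocks. Humidity, wind and precipitation are obtained (Environmental Data) but are not in the stage-1 covariate list. By the protocol's own assumption, weather of this kind is shared between sites. At stake is the interval around the main result of the primary objective.

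**Working it through.** **No figure to reproduce.** The protocol states no standard error, interval width, heterogeneity or cross-ED correlation for this analysis. What follows is a range under assumptions.

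**Inputs from the protocol**
- K = 56 EDs, about 6.35 million visits, 2019-2024.
- Days: 6 × 365 + 2 = 2,192.
- Mean visits per hospital-day: 6,350,000 / (56 × 2,192) = 51.7, if all 56 EDs contribute every day.
- Heat days (above the clinic-specific 95th percentile): 0.05 × 2,192 ≈ 110 per ED.

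**Assumed, not in the protocol**
- rho, the same-day residual correlation between EDs.
- r, the correlation of their heat-day indicators.
- Dispersion, and tau², the true between-ED variance.
- A binary heat contrast in place of the full lag model.

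**Formula.** Let s² be the stage-1 variance of one ED's estimate, and c ≈ rho × r the correlation between two EDs' estimation errors.
- True variance of the pooled estimate: [tau² + s²(1 + (K − 1)c)] / K.
- The expected spread between ED estimates is tau² + s²(1 − c), so the independence model estimates tau² as about max(0, tau² − c·s²) and reports [s² + max(0, tau² − c·s²)] / K.

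**Analytic results with r = 0.6.** With tau² = 0 the standard error (SE) ratio, true to reported, is √(1 + 55 × 0.6 × rho). With tau² = s² it is √[(2 + 33·rho) / (2 − 0.6·rho)]. At rho 0.05 these are √2.65 = 1.63 and √(3.65 / 1.97) = 1.36. The false-positive rate of a nominal 5% test is 2 × [1 − Φ(1.96 / ratio)]. With dispersion 1.5, the log-rate residual variance is 1.5 / 51.7 = 0.029, and the common daily swing has SD √(0.029·rho).

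| rho | SD of common swing | SE ratio, tau² = 0 | False positives | SE ratio, tau² = s² | False positives |
|---|---|---|---|---|---|
| 0.01 | 1.7% | 1.15 | 9% | 1.08 | 7% |
| 0.05 | 3.8% | 1.63 | 23% | 1.36 | 15% |
| 0.10 | 5.4% | 2.07 | 34% | 1.65 | 24% |

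**Simulation.** 56 EDs, 2,192 days, dispersion 2, heat-day overlap about 64%, DerSimonian-Laird pooling, 400 runs per cell (Monte Carlo error of a 95% coverage: √(0.95 × 0.05 / 400) = 1.1 points). Here s = √[(2 / 51.7)(1/109.6 + 1/2,082.4)] ≈ 0.019, so tau = 0.02 is close to tau² = s². Cells show the SE ratio and the coverage of the 95% interval.

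| rho | tau = 0 | tau = 0.02 | tau = 0.05 |
|---|---|---|---|
| 0 | 0.94 (97.2%) | 0.92 (96.0%) | 1.02 (93.2%) |
| 0.01 | 1.11 (92.2%) | 1.11 (91.8%) | 1.01 (95.0%) |
| 0.05 | 1.60 (77.2%) | 1.35 (85.2%) | 1.17 (90.5%) |
| 0.10 | 2.09 (65.5%) | 1.65 (77.2%) | 1.19 (89.0%) |

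**Overlap without residual correlation.** With identical heat days in all EDs, rho = 0 and tau = 0.02, the SE ratio was 1.03, coverage 92.8% and the ratio of estimated to true tau² 1.00. Shared heat days are not themselves the problem.

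**Heterogeneity.** The ratio of estimated to true tau² lay between 0.88 and 1.03 over all cells with tau > 0, including rho = 0.20. The lowest value came at rho = 0.20 and tau = 0.02.

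**Smooth time terms.** A further simulation with smooth time terms in stage 1 gave smaller SE ratios: about 1.1-1.3 at rho 0.05 and 1.35-1.65 at rho 0.10, and lower again when the correlation fell with distance.

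**The case against.** The strongest reply is that nothing here is shown to be wrong. The protocol does not say that EDs are treated as independent, it leaves detail to an analysis plan that is not shown, and it does not exclude a multilevel or robust second stage. It gives no rho, and stage 1 already removes seasonal, weekday and holiday variation common to the EDs. The largest ratios assume no true heterogeneity, whereas the protocol expects geographical differences. They also apply one correlation to every pair of EDs across Germany. In absolute terms the change may be modest: in a 150-run simulation at rho 0.05, the reported SE was 0.0025 against an actual 0.0038. The 95% half-width then goes from 1.96 × 0.0025 ≈ 0.5% to 1.96 × 0.0038 ≈ 0.75% of the visit rate, for a binary contrast rather than the planned curve.

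Most of this stands, and it limits the point to a conditional one. A reader might infer from the shared calendar that the interval is certainly too narrow. The documents do not support that, since harm needs residual correlation that they neither give nor exclude. A reader might also infer that between-site heterogeneity is materially understated. The calculations do not bear that out.

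What does not stand is that this is only omitted detail. Separate fits followed by random-effects pooling is a stated method. As described, it has no place for cross-ED covariance, and no listed covariate or sensitivity analysis deals with day-level shocks common to EDs.

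**Conclusion.** The point holds in conditional form. If same-day residuals remain positively correlated across EDs after the planned adjustment, the pooled interval for the primary heat effect will be too narrow. The size depends on rho, which is unknown. The understatement is small at 0.01 (SE ratio about 1.0-1.15). It can be material at 0.05 (about 1.1-1.6) and at 0.10 (about 1.2-2.1), because 56 sites multiply a small correlation. The low ends belong to marked true heterogeneity, to smooth time terms or to correlation that declines with distance. The high ends belong to no heterogeneity and a uniform correlation.

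These ranges rest on assumed rho, overlap, dispersion and tau, and on a binary contrast instead of the full lag model. They show sensitivity and do not forecast this study's error. That EDs share many heat days is a fair reading of the large-scale weather assumption, but no overlap figure and no site-to-station pairs are shown. No bias in the heterogeneity estimate is claimed.

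**What to change.** Keep the two-stage model and add one check and one conditional step to the analysis plan.

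1. After stage 1, estimate the same-date correlation of residuals across EDs, and report it overall and by distance between EDs.
2. Unless it is negligible by a limit set beforehand, take the pooled interval from a method that keeps calendar days together across EDs. Either use a calendar-block bootstrap that draws the same blocks of days for all EDs and repeats both stages, or estimate the cross-ED covariance of the stage-1 coefficients from same-date score residuals and supply the full matrix to the meta-analysis.

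No new data are needed. The cost is analysis-plan wording, computing time and possibly a somewhat wider primary interval. If the correlation proves negligible, the planned interval stands and the check documents why.

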#### Ancillary Prospective Geriatric Substudy (O6)

Analyses of the prospective geriatric substudy will be conducted separately from the retrospective registry-based analyses and follow prespecified endpoints and analytical procedures as defined in the substudy protocol and DRKS registration. We will summarize baseline characteristics and patient-reported and functional outcomes using appropriate descriptive statistics. Associations between heat exposure measures and substudy outcomes will be evaluated using regression models suited to the outcome scale (eg, linear, logistic, or ordinal models, as applicable), with effect estimates reported alongside 95% CIs. Models will adjust for key prespecified covariates available in the substudy dataset (eg, age, sex, and frailty-related measures), and sensitivity analyses will address missing data and loss to follow-up where appropriate.

#### Surveillance (O7)

To create the syndrome definition, a literature search on ED visits during heat events will be conducted to identify relevant *ICD-10-GM* and CEDIS-PCL codes. The feasibility and validity of the created syndrome definitions will then be assessed using the above-described retrospective ED data linked with environmental data. We will perform descriptive analysis of the identified cases of the health indicator of interest (eg, heat-related ED visits) using time series and exposure-outcome plots to visualize a potential association between the frequency of codes and temperature. Logistic regression analyses will be used to quantify these associations and account for uncertainty. The results will be discussed with clinical experts, and the syndrome definition will be adjusted in an iterative process until one indicator is finalized. To validate the indicator, time series of the syndrome definition will be compared with temperature time series, and mixed model logistic regression analyses will be conducted again to quantify the associations and uncertainty between trends of identified cases and changes in temperature. Furthermore, we will be looking into other external data sources, such as heat mortality and heat warnings from the DWD, to assess if we can perform additional validation analysis by comparing them with the heat indicator created in this study.

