#### Prediction Model (O8)

The objective is to develop mathematical models using machine learning methods to enable simulation-based analyses, such as weather-dependent predictions. These models will vary in granularity and capture correlations between environmental data and disease-specific demographic factors, such as age and sex. Feature selection will be tailored to different disease types, incorporating demographic characteristics and clinical patient information. Based on this analysis, customized data-driven machine learning models will be developed. Various model types, including support vector machines, feedforward neural networks, and recurrent neural networks, will be explored. The proposed architectures were selected based on their strengths for the prediction task at hand: support vector machines provide robust performance in high-dimensional feature spaces with strong regularization properties; Feedforward neural networks offer flexibility in modeling complex nonlinear relationships between environmental and demographic variables; and recurrent neural networks are specifically suited for capturing temporal dependencies and lagged effects inherent in time series data such as seasonal ED usage patterns. These models will be trained and cross-validated using supervised learning on ED data. A literature review will be conducted to identify models that integrate expert knowledge, with a particular focus on time series models incorporating climate data for forecasting ED usage. An initial approach may involve time series regression with climate variables, allowing for the prediction of seasonal trends. Additionally, daily aggregated environmental data (see section *Data Linkage*) will be incorporated into the modeling process. This dual approach mitigates project risks by combining machine learning as a black-box model with an interpretable time series approach. The integration of both methodologies will enhance insights, particularly in feature selection. To ensure reproducibility, all source code will be made publicly available via the project’s GitHub repository [35].

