### Dissemination

Findings of the study will be made available as oral or poster presentations at scientific conferences, through publications in peer-reviewed journals, and will be shared with relevant clinical, public health, and policy stakeholders. In addition, resource and care relevant results related to ED overcrowding, patient referral, and morbidity that are derived from the health care research analyses, including validated syndromic surveillance, and from prediction modeling, will be presented to participating EDs through an interactive web application. Using the application, the EDs should be able to estimate what usage can be expected under the assumption of certain weather constellations.

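### The heat indicator (O7) is tuned on its association with temperature and then validated on that same association, with no separate data named, so the validation is not independent of the tuning

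*Protocol article*

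**What the plan says.** The protocol article, Statistical Methods, Surveillance (O7), sets out this sequence:

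- **Candidate codes** come from outside the study data: "a literature search on ED visits during heat events will be conducted to identify relevant" diagnosis and complaint codes.
- **Assessment:** "The feasibility and validity of the created syndrome definitions will then be assessed using the above-described retrospective ED data linked with environmental data". The tools are time series and exposure-outcome plots to "visualize a potential association between the frequency of codes and temperature", followed by logistic regression.
- **Revision:** results go to clinical experts, and "the syndrome definition will be adjusted in an iterative process until one indicator is finalized". The number of rounds and the stopping rule are not given.
- **Validation, first part:** "To validate the indicator, time series of the syndrome definition will be compared with temperature time series".
- **Validation, second part,** a repeat of the regression from the assessment step: "mixed model logistic regression analyses will be conducted again to quantify the associations and uncertainty between trends of identified cases and changes in temperature".
- **External sources:** heat mortality and weather-service heat warnings will be looked into, to see whether a further validation is possible.

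Two other sections bear on this. Outcomes, Syndromic Surveillance (O7), says without condition that the performance of the definitions will be validated against different reference data sources. Dissemination says that results including "validated syndromic surveillance" will be shown to participating EDs in a web application.

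**The concern.** Validation should be able to fail an indicator that tuning has passed. Here both steps ask the same question: does the frequency of the coded visits move with temperature? If both also use the same visits, a code that rose with temperature by chance is more likely to survive revision. The same chance then counts in its favour at validation. The reported association would be too strong and its confidence interval too narrow.

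The one check that could break the circle, a reference other than temperature, is a promise under Outcomes and only a possibility under Statistical Methods. EDs are to receive the result under the label validated, so they could read an in-sample association as independent evidence of performance.

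**Working it through.** **1. The two steps side by side**

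| | Tuning | Committed validation |
|---|---|---|
| Data | Retrospective ED data linked with environmental data | No other data named |
| Criterion | Association with temperature | Association with temperature |
| Method | Plots, logistic regression | Time-series comparison, mixed-model logistic regression, run *again* |
| Reference other than temperature | None | Conditional only |

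The article gives no sample size, error rate or performance target for O7, so there is no figure of the plan's own to reproduce. The steps below show what reuse of the data does.

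**2. Chance that an all-null indicator passes**

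Assumptions, none of them given in the documents: K candidate codes of equal frequency, independent, with no temperature effect. Each has a statistic z ~ N(0,1) for its association with temperature. A pruning rule keeps m codes. The pooled indicator has Z = (sum of the kept z)/√m and passes if Z > 1.96 (nominal 2.5%). There were 20,000 runs per setting.

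| K | Drop worst 20% once, same data | Keep only z > 0, same data |
|---|---|---|
| 5 | 7% | 14% |
| 10 | 12% | 36% |
| 20 | 25% | 79% |
| 50 | 59% | 100% |
| 100 | 90% | 100% |

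On independent data, every K and rule gave 2.4–2.7%. With no data-driven pruning, the same-data rate was 2.4–2.8%. The excess therefore comes from selecting and testing on the same data.

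Hand check: under the rule z > 0, a kept code has mean √(2/π) = 0.798 and about K/2 codes are kept, so the mean of Z is about 0.798 × √(K/2). For K = 20 this is 0.798 × √10 = 2.52 (simulated 2.50). For K = 50 it is 0.798 × √25 = 3.99 (simulated 3.98).

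**3. The same check with daily counts**

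This used Poisson counts over 2,192 days (2019–2024), a seasonal autocorrelated temperature series, the rule of keeping positively associated codes, and 400 runs. Reusing all days, the all-null indicator passed in 32% (K = 10), 82% (K = 20) and 100% (K = 50) of runs. Tuned on 2019–2022 and tested on 2023–2024, it passed in 2.3–2.5%.

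**4. Size of the spurious odds ratio**

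Here null codes are ranked by their share of cases on heat days (5% of days), and the kept set is evaluated on the same data. Code counts are drawn log-uniformly.

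| Cases per code (assumed) | Keep top 10 of 60 | Drop worst 20% of 20 |
|---|---|---|
| 20–635 | 1.69 | 1.06 |
| 200–6,350 | 1.21 | not run |
| 635–6,350 | 1.15 | 1.02 |
| 2,000–20,000 | 1.09 | not run |
| 6,350–63,500 | 1.05 | 1.01 |

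The true odds ratio is 1.00 throughout. A large bias needs rare codes and hard selection together. With common codes or light pruning it is small.

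**The case against.** The best defence is that the procedure is not blind data mining. Codes come from published work on heat events, and revisions follow discussion with clinical experts. No step is described that ranks codes by odds ratio or keeps a best subset. A set of codes with no heat signal at all is therefore unlikely, and the rates above are for that worst case. O7 is also listed among the exploratory objectives, and the article leaves analytical decisions to an analysis plan that is not shown and that could specify a data split.

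Much of this stands. A reader might infer that the indicator will look good even if its codes carry no heat signal. The text does not support that: the literature and expert steps work against it, and light pruning of a few codes inflates the pass rate only to 7–12%. Reuse of the same data is the natural reading of a section that names one dataset and repeats the regression, but a split is not excluded.

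Two further inferences should not be drawn:

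- **Season.** The O7 section lists no covariates at all, so it does not follow that season will be ignored. The O1–O5 models do adjust for it.
- **Prediction models (O8).** "These models will be trained and cross-validated using supervised learning on ED data" does not say how folds are formed, and time-blocked schemes are also cross-validation. Leakage between neighbouring days cannot be read from it. Dissemination also attaches the word validated to the surveillance only, not to the forecasts.

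What the defence does not answer is that the article itself states the validation method. Even with a split, temperature association would be both the design target and the proof unless the external comparison becomes a commitment. The difference between Outcomes and Statistical Methods on that comparison remains whatever the analysis plan says.

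**Conclusion.** The point holds in a limited form. As written, the committed O7 validation is not independent of the tuning. It will tend to be optimistic and cannot be relied on to expose codes kept by chance. It does not follow that the final indicator will be spurious.

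The size cannot be fixed from the documents. The number of codes, their frequency, the severity of pruning and the reuse of all data are assumptions. Across the settings tried, an all-null indicator passes a nominal 2.5% test in about 7% to 100% of runs, against about 2.5% on independent data. The spurious odds ratio runs from about 1.0 to 1.2 in most settings and is larger only for rare codes under hard selection.

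Separately, Outcomes and Statistical Methods disagree on whether reference-source validation is promised or only possible, and Dissemination assumes it has succeeded. The matter should be corrected, but it concerns an exploratory objective and leaves the primary analysis untouched.

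**What to change.** 1. Develop the definition on a subset of years, sites or both (for example 2019–2022), freeze it, and test it once on the unused part. Fix the split before tuning uses all the data.
2. State that the O7 models use the seasonal adjustment already planned for O1–O5. A split alone would not remove a shared summer peak, which recurs in the held-out years.
3. Commit to at least one reference that is not temperature itself. Heat mortality, which the article already names, is the clearer choice. Weather-service heat warnings are better as a supplement, since they are probably driven by temperature (an assumption; the article does not say how they are issued).
4. Align Outcomes, Statistical Methods and Dissemination on what validation is promised. If steps 1 and 3 are not taken, drop the word validated and describe the indicator as developed and explored.

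The split needs no new ED data: six years and 56 EDs are available. The cost is wording, obtaining the external series, and fewer cases for developing rare codes. Holding out 2023–2024 sets aside 731 of 2,192 days, or 33%.
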